## Abstract

**Introduction:**

Around 80% of the world’s smokers live in lower-middle income countries and smoking rates in China, Philippines and Indonesia are very high. Evidence suggests that most people begin smoking or become habitual smokers before reaching adulthood. This highlights the need for a smoking prevention intervention focused on young people. ASSIST (A Stop Smoking In Schools Trial) is a ‘peer-led’, school-based smoking prevention intervention, shown to be effective in the UK. The aim of the study is to assess the feasibility of conducting a full-scale effectiveness evaluation of an adapted version of the ASSIST intervention in China, Indonesia or the Philippines. However, due to issues with obtaining relevant approvals, China was removed from the trial with the approval of the funder and Trial Steering Committee, and the study will only be completed in Indonesia and the Philippines.

**Methods and analysis:**

A feasibility mixed-methods cluster randomised controlled trial in 10 schools (six intervention, four control) in each of the two countries. Participants will be students aged c13–14 in mainstream (‘lower secondary’) schools. In addition to their usual education on smoking, intervention schools will receive the ASSIST intervention which is based on ‘diffusion of innovation’ theory, with new norms and behaviours promoted through: (1) peer modelling by locally influential individuals; and (2) information disseminated by them through their social networks. Control schools will continue with their usual education around smoking prevention.

The key outcome of the study is whether prespecified progression criteria relating to recruitment, retention, acceptability and feasibility have been met in order to progress to a larger cluster randomised controlled effectiveness trial in one or more of the countries. A mixed-methods process evaluation will assess acceptability, feasibility and fidelity of intervention delivery, exposure to and reach of the intervention. The feasibility of trial processes including outcome measurement will be assessed. An economic evaluation will estimate the costs of the ASSIST intervention. Statistical analyses will focus on feasibility criteria, and qualitative data will be analysed using a framework approach. Outcomes assessed will include self-reported smoking behaviour (own and that of friends and family); vaping and other forms of nicotine use; smoking-related attitudes and knowledge; smoking norms; self-esteem; self-efficacy; (all at baseline and 7 month follow-up) and exhaled carbon monoxide concentration (at follow-up only).

**Ethics and dissemination:**

The trial has been approved by the University of Glasgow College of Medical, Veterinary and Life Sciences (MVLS) Ethics Committee (ref: 200210204), the De La Salle University Research Ethics Review Committee (ref: 2023-012C) and the Medical and Health Research Ethics Committee (MHREC); Faculty of Medicine, Public Health and Nursing; Universitas Gadjah Mada (ref: KE/FK/1205/EC/2022). The trial is sponsored by the University of Glasgow (Head of Research Regulation and Compliance—[contact]). The sponsor will not have input in data collection, management, analysis and interpretation; write up and submissions for publication.

The study findings will be disseminated through peer-reviewed publications in expert journals and conference presentations and targeted communications to schools, policymakers and the public.

**Trial registration number:**

ISRCTN99140476.

STRENGTHS AND LIMITATIONS OF THIS STUDYThe study includes a mixed-methods process evaluation which will provide rich triangulated data to inform questions of feasibility and acceptability as well as required contextual adaptations.The intervention being tested is theory based, and we will update and refine the programme theory as part of this study.A limitation of the study is that blinding of participants and intervention delivery staff will not be possible.This feasibility trial is not designed to identify an estimate of effect and thus a standard power calculation is not appropriate.

## Introduction

 Tobacco is the world’s leading cause of avoidable poor health and premature death.^1^ In higher-income countries, tobacco use peaked in the 1960s/1970s, falling as tobacco control programmes were introduced in recognition of its health harms.^2^ Around 80% of the world’s smokers live in low-income and middle-income countries (LMICs). ^3 4^This study is set in Indonesia (population 277 million) and the Philippines (population 117 million), both are LMICs in South East Asia, but they have very different cultural and contextual influences. In the Philippines, Christianity is the main religion (89%) and in Indonesia, 87% of the population are Muslims. In the Philippines, school is compulsory for 13 years from age 5 and in Indonesia, it is compulsory to attend 12 years of schooling. According to the World Bank, in 2024, the poverty rate is 9% in Indonesia and 15.5% in 2023 in the Philippines.^1^

The prevalence of smoking in Indonesia and the Philippines is high, with the latest available data on current tobacco use in those aged 15 years and older (male/female) reported in 2021 as: Indonesia 60.4%/1.8%; Philippines 41.6%/6.5%.^1^ The most recent surveys from 13 to 15 year olds again highlight high male rates in the two countries: rates of any tobacco use in males/females of 35.6%/3.5% in Indonesia^5^ and rates of any cigarette smoking of 18.3%/6.9% in the Philippines.^6^ Prevalence rates vary in LMICs for under 15 s, it is estimated on average that 13.6% of 12–15 year olds are current smokers (defined as smoking on at least 1 out of the past 30 days).^7^

High adult smoking rates and strong smoking cultures mean large numbers of family members smoke, and although health risks may be acknowledged, smoking is often viewed as the norm, including as a masculine rite of passage.^8^,^10^ Cigarette advertising is permitted in some settings in Indonesia,^11^ while the Philippines have adopted stronger policies in the past decade.^12^,^14^ There are few or no smoking cessation programmes for adolescents in these countries.^15^ However, while tobacco control policies are crucial, public health practitioners recognise the need for interventions at *multiple* socioecological levels.^16^

The very high smoking rates in the two countries highlight the need for *youth* prevention, given evidence that few people begin smoking or become habitual smokers in adulthood.^17^ While both countries have smoke-free school rules, there are variations in enforcement and in the provision of school-based smoking prevention programmes. When implemented, these programmes are often infrequent, inconsistent and adult-led, which are less effective than those led by peers.^15^ Most people begin smoking before the age of 18.^18^ Research shows those who begin smoking during adolescence are more likely to become habitual smokers in adulthood.^19 20^ Therefore, earlier interventions are needed to prevent people from starting to smoke when they are young and reduce future adult smoking rates. ASSIST (A Stop Smoking In Schools Trial) is a ‘peer-led’, school-based smoking prevention intervention, developed in the UK and shown to be effective in preventing adolescent smoking uptake^21^ when the UK had insufficient tobacco control measures, and high rates of smoking, which were rising in females^22^—similar to the current situation in the study sites. ASSIST is based on ‘diffusion of innovation’ theory, with new norms and behaviours promoted through: (1) peer modelling by locally influential individuals; and (2) information disseminated by them through their social networks. ASSIST became a licensed programme in 2010 and has been made widely available via a not-for-profit company, ‘Evidence-to-Impact Ltd’ (https://evidencetoimpact.com/).

## Aims and objectives

The primary aim of the study is to assess the feasibility of conducting a full-scale effectiveness evaluation of an adapted version of the ASSIST intervention in one or more of the three LMICs. As originally planned, the study was to take place in China, Indonesia and the Philippines. However, due to issues with obtaining relevant approvals, China was removed from the trial.

Secondary objectives are to assess, for each country:

What, if any, *adaptations to ASSIST* as previously delivered in the UK are required for its delivery in these countries given the different cultural, political, social and educational systems?Is the intervention *feasible and acceptable* to peer supporters, participants and key stakeholders (school staff, education policymakers and parents)?What is the *fidelity and reach* of intervention delivery by trainers and peer supporters, including barriers to, and facilitators of, successful implementation?What is the density, breadth and strength of links within the social networks of each year group, and does this differ between the countries?Does the clustering of smoking within social networks differ across the countries?To what extent are smokers ‘popular’ within each year group, and does this vary by country?Does peer supporters’ ability to reach the whole year group depend on characteristics of the peer supporter, the network structure or the country?What is the reach of peer supporters to ‘at risk’ students?Do the social ties of peer supporters change over the course of the intervention?Are there cross-country differences in the mechanisms of peer selection and influence on smoking?Are we able to recruit and retain schools and peer supporters?Is the evaluation design feasible and acceptable?How applicable are ‘western’ or higher-income country exhaled-breath carbon monoxide (eCO) values in determining active smoking within these countries (given that populations are likely exposed to higher ambient carbon monoxide concentrations from industrial pollution and/or heating and cooking sources of carbon monoxide at home)?Can we collect the required data needed to cost the intervention and conduct a cost-effectiveness analysis?Is there any evidence of social harms (negative social influences, impacts on peer relationships or victimisation) or unintended consequences as a result of the intervention?Is there policy interest in providing (or redirecting) financial support for the intervention to be tested in a future trial and subsequent roll out should a future trial show it to be effective?

## Methods and analysis

This protocol is reported in accordance with the Standard Protocol Item Recommendations for Interventional Trials (SPIRIT) 2013 guidance and outcomes 2022 checklist^23 24^ (online supplemental file 6).

### Trial design

The trial is a feasibility cluster randomised controlled trial, with nested process and economic evaluation. Planned start and end dates are 1 March 2022 and 30 December 2025, respectively. The trial will be conducted in 10 schools (six intervention, four control) with between 100 and 500 students per school in each of the two countries (Indonesia, the Philippines). Schools will be randomly allocated to intervention (n=6) or control (n=4). Figure 1 summarises the proposed study flow.

**Figure 1 F1:**
[figure not shown]
ASSIST global study flow chart. ASSIST, A Stop Smoking In Schools Trial.

### Trial setting

Private and public schools in the Philippines and Indonesia located in Yogyakarta City and Magelang District in Indonesia; and in and around Manila city in the Philippines.

### Trial participants

Ten secondary schools will be recruited in each country. Depending on the availability of relevant data, we will attempt to specifically target schools in areas of lower socioeconomic status and with high smoking rates. Each year group size will be between 100 and 500 students (mean c.333), so there will be approximately 4000 students in intervention schools and 2666 students in control schools overall. ASSIST is a whole school year-group intervention, thus all students in the target school year (aged 13–14 years) in each country will be potentially eligible to participate in the intervention and research. Students in the target school year who are outside of the 13–14 age group will not be excluded, as students in the target class in Indonesia may be age 15 by public school regulation, and some students in the Philippines may have had to pause or delay their studies due to socioeconomic hardship or challenges in completing their schoolwork.

#### Inclusion criteria

State and privately funded schools.All students in the target year group who are enrolled for school (whether smokers, non-smokers, or experience of smoking).

#### Exclusion criteria

##### Schools

Schools with school year groups smaller than 100 or greater than 500 will be excluded.Schools with limited or poor internet if the study is required to run remotely if COVID situations dictate.No single-sex schools (due to the low rates of girls smoking in some countries and also the important influence of the opposite sex on smoking behaviour).

##### Individual students

Any student identified by the researchers, in consultation with teaching staff, as not having the mental and emotional capacity to consent and fully engage in the research will not be excluded. If a change in mental or emotional capacity occurs during the study, making it difficult for students to take part, then they can be withdrawn from the research process on advice from teaching staff.Other reasons for student ineligibility to consent may include learning difficulties, level of literacy and language comprehension issues.

### Randomisation

We will recruit schools for data collection and use cluster randomisation at the school level, with schools being randomised to the intervention or control arms (six intervention and four control) in each country after we have collected their baseline data. Stratification by school year size and a measure of a school’s overall academic performance will be used to reduce the potential for any sizeable differences between intervention and control arm baseline characteristics. Randomisation will be conducted by a member of staff at the University of Glasgow who is independent of the national study teams.

In the Philippines, schools will be stratified by their ‘grade 8 year group size’ and by their NAT score (National Achievement Test; a standardised set of examinations taken by all students). Schools will then be paired into four groups of two to three schools, and within each group, one school will be randomised into the control group, with the remaining schools in each group being assigned to the intervention group.

In Indonesia, a similar process will be followed, but two different measures of school’s academic performance will be used due to differences in how the Yogyakarta City and Magelang Regency regions measure the academic performance of schools. Students in Yogyakarta City undertake a set of standardised examinations known as ‘ASPDs’, whereas in Magelang Regency, the school authorities are not sharing exact academic performances of schools and instead will provide subjective rankings for the five schools in the region taking part in the trial. These subjective rankings will be based on overall academic and non-academic (sports and arts) achievement reports submitted to them by schools. In each region, the five schools will be stratified by school size and by the relevant academic performance measure into two groups of two to three schools, with one school in each group being randomised to the control group and the remaining schools in each group being assigned to the intervention group.

### Consent

Consent to participate in the study will be collected from schools, parents, students and trainers (see figure 2 for summary of who provides consent and when at each stage of the study). Initial consent will be obtained from schools to participate in the ASSIST global project by signing a Partnership Agreement. Schools will then disseminate information about the study to parents so they can decide whether to allow their children to participate in the study. Parents will be given a form with the information sheet which they can complete if they wish for their child not to participate in the study (opt out consent) (online supplemental file 1). Students whose parents do not return the slip will be invited to participate in the study using an opt-in consent procedure (ie, the students actively decide to take part) (online supplemental file 2).

**Figure 2 F2:**
[figure not shown]
ASSIST global consent flow diagram. Blue, opt-out consent; Red, opt-in consent. ASSIST, A Stop Smoking In Schools Trial.

### The intervention group

In the initial stages of the study, we will conduct stakeholder work with policymakers, principals, teachers and students to refine the intervention to allow tailoring to the country contexts. We will also recruit trainers who will be trained to deliver the intervention. The training will be piloted in one school, and the trainers will receive feedback.

Schools in the intervention arm will receive the ASSIST intervention in addition to the usual school education on smoking. Peer supporters will be recruited from among the target year group who have been voted as ‘most influential’ by their year group via a short questionnaire. Around 18% of the students who receive the most nominations, stratified by gender, will be invited to a recruitment meeting. Those who choose to take on the role will attend a 2 day training course run by the trainers. Over a defined period of 10 weeks, peer supporters will use social media and face-to-face interaction to disseminate messages aimed at preventing smoking. They will encourage their friends/peers in their year group not to take up smoking. They will be supported—through regular meetings and via social media—by the professionals who trained them. They will also have access to ASSIST global resources (assistglobal.net which is adapted for each country and a moderated forum) for further support. Although only about 18% of the cohort will be trained to be peer supporters, the effect of the programme is likely to be seen across the year group as the remaining students will receive the intervention via informal interactions initiated by the peer supporters.

The ASSIST global programme theory is summarised in the logic model below (figures3  4) and was adapted from the STASH study.^25^

**Figure 3 F3:**
[figure not shown]
ASSIST global logic model. ASSIST, A Stop Smoking In Schools Trial.

**Figure 4 F4:**
[figure not shown]
ASSIST global logic emodel (continued). ASSIST, A Stop Smoking In Schools Trial.

### The control group

Control schools in each country will continue with their usual education around smoking.

School-based smoking prevention programmes in Indonesia use the School Health Unit (Usaha Kesehatan Sekolah/UKS) to improve students’ overall health status through the implementation of the Trias UKS. UKS aims to reduce youth smoking rates by increasing students’ awareness of the dangers of smoking and vaping; creating a supportive school environment through regulations and health promotion efforts including no-smoking policies for students and the installation of educational posters and providing smoking prevention and cessation support for students who have already started smoking.^26^ However, the implementation of smoking prevention initiatives through health promotion, as mandated by government regulations, remains suboptimal. According to the Global Youth Tobacco Survey (GYTS) 2009, only 69.3% of students received information about the dangers of smoking at school.^5^

In the Philippines, the Department of Health implements programmes designed to inform the population about non-communicable diseases and target substance abuse, which are accessible through residential communities and publicly funded schools.^27^ It also created the Adolescent Youth Health subprogramme composed of government and non-government units working on addressing health issues specific to adolescents, with the overarching goal to improve the health status of adolescents through provision of prevention services that focus on health education and building life skills—creating a system that increases knowledge and changes behaviour that leads to the avoidance of risky behaviours and increases practice of protective behaviours, and utilisation of services.^28 29^ The Department also implements Barkada Kontra Droga, a programme intended to dissuade young people from substance use, promoting a drug-free and productive life through activities such as youth camps, seminars and competitions.^30^

The activities vary by country and also across schools, but we will capture details of this as part of the process evaluation. At the end of the study, we will offer something to the control group schools such as resources and talks by the study team.

### Retention of participants

On receipt of the signed Partnership Agreement, the school will be considered formally recruited to the study. Any school opting to discontinue with the study after this point will be considered a withdrawal. To maximise retention, schools will be given compensation for disruption to school life due to the questionnaire and process evaluation activities.

Given the whole year-group nature of ASSIST, individual opt-out from the intervention will not be possible. However, those nominated as influential and invited to become peer supporters have the right to withdraw consent for this at any time, as do all those participating in any aspect of the research process. If a participant initially consents but subsequently withdraws from the study, a clear distinction will be made as to what aspect of the study the participant is withdrawing from.

Leaflets detailing the benefits of becoming a peer supporter have been developed to maximise parental consent for students to sign up as peer supporters. Small reimbursements (gifts/vouchers) will be provided to those involved in the data collection as well as research interviews/focus groups (school staff, students and parents). This will vary by country; drinks and healthy snacks may also be provided during group consultation or research sessions.

### Outcome measures and progression criteria

The primary outcome of this feasibility trial will be to assess whether prespecified progression criteria are met to progress to a full effectiveness trial of the ASSIST intervention. The country-level progression criteria are described in online supplemental table 1. These have been approved by our independent Trial Steering Committee (TSC). Final assessment of the progression criteria will be undertaken by the independent TSC in collaboration with the Trial Management Group (TMG), following analysis of the findings.

Outcome data will be collected at baseline (prerandomisation) and 7 month follow-up postrandomisation (see table 1 for an overview of outcome measures at each timepoint). In-country researchers will distribute questionnaires to the whole year group in all schools. At baseline, this will be completed after the peer nomination, which will happen on the same day in all schools. The baseline questionnaire (onlinesupplemental files 3  4) will gather the outcomes listed in table 1 as well as additional data known to be related to smoking. At the 7 month follow-up, we will repeat the same questionnaires but also use a standard objective method of assessing recent active smoking: eCO using a Smokerlyzer Micro+device.

**Table 1 T1:** Outcome measures and effect modifiers

Outcome/effect modifier	Timepoint	Measured by
Smoking behaviour (own and that of friends and family including spillover effects)	Baseline and 7 months	Study developed questionnaire
e-cig/vaping and other forms of tobacco use	Baseline and 7 months	Study developed questionnaire
Smoking-related attitudes and knowledge	Baseline and 7 months	Study developed questionnaire
Smoking norms	Baseline and 7 months	Study developed questionnaire
self-esteem	Baseline and 7 months	Study developed questionnaire
Sociodemographics	Baseline only	Study developed questionnaire
eCO	7 months only	Smokerlyzer Micro+

eCO, exhaled-breath carbon monoxide.

The primary effectiveness outcome is self-reported weekly smoking (ie, those reporting they smoke 1+cigarettes weekly) measured via the study questionnaire at baseline and 7 month follow-up. Informed by our programme theory, we will investigate a range of secondary outcomes and effect modifiers as listed above. The study questionnaire is based on the original ASSIST trial questionnaire with adaptations (ie, socioeconomic questions tailored to be locally relevant) and updates (eg, vaping questions).^21 31^

We will also do some exploratory work looking at concentration thresholds for eCO to examine the level of agreement between self-reported smoking and measured eCO concentrations. The traditional ‘cut-points’ for identifying smoking (0–6 ppm: non-smoker; 7–9: borderline; 10+: active smoking) have been developed in ‘western’ countries where outdoor air concentrations of CO tend to be low and where indoor combustion of fuels (eg, coal, wood and kerosene) is uncommon and rarely leads to high exposure. In countries where outdoor and indoor concentrations of CO are higher, it is possible that non-smoking children will have eCO levels that exceed the standard indicative values for active smoking.^32^

There is a possibility that we will identify high readings of carbon monoxide on the Smokelyser device even when children claim that they are not smoking. This may be caused by exposure to poorly ventilated or simple cooking/heating systems. In this case, we will give the children a letter to take home to their parents advising them to check the safety of household heating and/or cooking arrangements. Outcome data will be collected from all participants who discontinue or deviate from the intervention protocol as long as they are willing.

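### Agreement with post-intervention self-report cannot by itself show whether western eCO cut-points apply, because it does not separate ambient carbon monoxide from denied smoking

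*Protocol article*

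**What the plan says.** All references are to the protocol article.

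- **Question.** Aims and objectives asks how applicable western eCO values are for detecting active smoking, given that "populations are likely exposed to higher ambient carbon monoxide concentrations from industrial pollution" and from home heating and cooking.
- **Method.** Outcome measures and progression criteria describes exploratory work on eCO thresholds to "examine the level of agreement between self-reported smoking and measured eCO concentrations". It gives the conventional bands as 0–6, 7–9 and 10+ ppm. Self-report is the only comparator named, and the article describes no ambient or household carbon monoxide measurement.
- **Timing and coverage.** The abstract lists "exhaled carbon monoxide concentration (at follow-up only") and Table 1 agrees. On coverage, "In-country researchers will distribute questionnaires to the whole year group in all schools"; at 7 months "we will repeat the same questionnaires but also use a standard objective method of assessing recent active smoking". No restriction to one arm is given.
- **Blinding.** The strengths and limitations box says "blinding of participants and intervention delivery staff will not be possible". Six of ten schools per country receive the programme (Trial design).
- **High readings with denied smoking.** The same outcome section says these may come from cooking or heating systems. It does not mention under-reporting.
- **Place in the analysis.** The abstract and Table 1 list eCO among the outcomes. The secondary outcomes named under Efficacy outcomes do not include it. Quantitative analysis says a detailed SAP has been drafted.

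**The concern.** The objective concerns the false-positive rate of a cut-point among true non-smokers exposed to ambient carbon monoxide. The stated method measures something else: how often eCO and self-report coincide. The two match only if declared non-smokers are true non-smokers. Here the declaration comes from 13–14 year olds at school, after an anti-smoking programme in the intervention arm.

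Concealed smokers among the declared non-smokers push the apparent non-smoker range upward. If a threshold were then moved up to improve agreement, part of the shift would reflect denial and not air quality, and the answer on this objective would be biased.

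eCO is also the only objective measure bearing on whether self-reported weekly smoking, the primary effectiveness outcome, is reported differently in the two arms. Overall agreement is a poor instrument for seeing that.

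**Working it through.** **Counts.** The article's figures reproduce: 2 × 6 × 333 = 3,996 (stated as about 4,000) and 2 × 4 × 333 = 2,664 (stated as 2,666). Per country this is about 1,998 intervention and 1,332 control students. No precision is stated for the eCO work.

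**Identification.** Let p be true smoking prevalence, r the share of smokers who admit it, s the share of smokers above the cut-point, and f the share of true non-smokers above it from ambient exposure. Assume no over-reporting. The expected cells are:

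- declared smoker, high eCO: p·r·s
- declared smoker, low eCO: p·r·(1−s)
- declared non-smoker, high eCO: p(1−r)s + (1−p)f
- declared non-smoker, low eCO: the remainder

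Three free cells cannot determine four unknowns, whatever the sample size.

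**Illustration (assumed inputs).** Take self-reported prevalence 8%, s = 0.7 and 5% of declared non-smokers above the cut-point. The cells are 0.056, 0.024, 0.046 and 0.874. Agreement is 0.056 + 0.874 = 93.0%. Chance agreement is 0.08 × 0.102 + 0.92 × 0.898 = 0.834, so kappa = (0.930 − 0.834)/(1 − 0.834) = 0.577 (unrounded inputs). With p = 0.08/r and f = [0.046 − p(1−r)s]/(1−p):

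| r | p | p(1−r)s | f |
|---|---|---|---|
| 1.0 | 8.0% | 0 | 5.0% |
| 0.8 | 10.0% | 0.0140 | 3.6% |
| 0.6 | 13.3% | 0.0373 | 1.0% |

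All three rows give the same table, agreement and kappa. At self-reported prevalence 5%, f runs from 5.0% to 2.6% as r goes from 1.0 to 0.6 (kappa 0.497 throughout). At 13.6%, the article's LMIC figure for ages 12–15, f runs from 5.0% to 0.3% as r goes from 1.0 to 0.7 (kappa 0.645 throughout).

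**Differential reporting by arm (assumed inputs).** Take p = 10%, s = 0.7, f = 3% in both arms, no true effect, and admission of 90% in control and 70% in intervention schools.

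- Self-report risk ratio: 0.07/0.09 = 0.78.
- High eCO among declared non-smokers, intervention: (0.021 + 0.027)/0.93 = 5.2%.
- High eCO among declared non-smokers, control: (0.007 + 0.027)/0.91 = 3.7%.
- Agreement pooled over arms: 93.4%, against 93.9% if both arms admit 90%.

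At p = 5% the arm contrast is 4.0% v 3.4%; at 13.6% it is 6.0% v 4.0%. A by-arm table shows the signal, while pooled agreement barely moves.

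**Precision of that by-arm contrast.** With 1,998 v 1,332 students (slightly generous, as not all are declared non-smokers), the SE at p = 10% ignoring clustering is √(0.0516 × 0.9484/1,998 + 0.0374 × 0.9626/1,332) = 0.0072. The difference of 0.0143 is 2.0 SE. With an assumed ICC of 0.01, the design effect is 1 + 332 × 0.01 = 4.32, and 2.0/√4.32 gives about 1.0 SE. At p = 5% the figures are 1.0 and 0.5 SE; at 13.6% they are 2.6 and 1.3 SE.

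**How much of a high-reading rate could be denial.** If 6% smoke and 30% of them deny it, concealed smokers are 0.018/(0.94 + 0.018) = 1.9% of declared non-smokers. If 4% of declared non-smokers read high, the share due to denial is at most 1.9/4 = 47%, and that needs every denier to exceed the cut-point. At s = 0.7 it is 33%; at s = 0.4 it is 19%. With denial of 50% in intervention and 30% in control schools, reported smoking is 3.0% v 4.2%, a risk ratio of 0.71 with no true effect.

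**The case against.** The strongest reply is that the article is condensed, the SAP exists but is not shown, and tables by arm are SAP-level detail. That stands as far as it goes. A reader might infer that the plan leaves out any check on differential reporting, or will not use eCO for one. The documents do not support this: eCO is a listed outcome, the outcomes section says the listed measures will be investigated, and a by-arm comparison is possible with the planned data. All that can be said is that the article states no such check.

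Three other tempting inferences are also unsupported:

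- **Pooling over arms.** The article does not say agreement will be pooled, and its secondary objectives are framed by country.
- **Weekly smoking as the eCO reference.** The article speaks of self-reported, active or recent active smoking and fixes no definition. A low reading in a once-a-week smoker is a caution for interpretation, not a fault in a stated choice.
- **A revised threshold carried into a full trial.** The article promises exploratory work and says nothing about adopting a new cut-point.

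It is also fair that the article itself raises ambient carbon monoxide, discloses the lack of blinding, and mentions cooking and heating only as a possible cause, in connection with a letter to parents. A by-arm contrast would be imprecise, and ambient exposure varies by place, so chance imbalance with 6 v 4 schools is plausible. Any group of unlikely smokers is still picked by self-report.

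None of this answers the identification problem. Self-report is the only reference stated, and agreement with it does not separate the two explanations.

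**Conclusion.** The point holds in a limited form. Agreement between eCO and post-intervention self-report cannot, on its own, show whether western cut-points apply in these countries. Under the stated assumptions, one observed table fits ambient false-positive rates from 5.0% down to 1.0%, depending only on how many smokers deny. A cut-point raised to improve agreement could absorb concealed smoking.

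The risk ratio of 0.71 and the share of about one half are illustrations under assumed denial rates, and the half is an upper bound. All values of p, r, s, f and the ICC are assumptions, except the 13.6% prevalence.

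Severity is low: the work is labelled exploratory, and the trial is a feasibility study not designed to estimate effect. The change is still worth making, because it is cheap and the applicability of eCO values is a listed objective.

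**What to change.** In the SAP, within each country:

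1. Describe the eCO distribution among declared non-smokers in control schools. Add a sensitivity analysis in those least likely to be concealed smokers (non-smokers at both waves with no smoking friends), with girls shown separately, since the Introduction reports low use among them. State that this group is still chosen by self-report and may differ in household exposure.
2. Report by arm the share of declared non-smokers above the cut-point, with cluster-aware confidence intervals. Read a difference as suggestive evidence of differential under-reporting only, because ambient exposure may be unbalanced with 6 v 4 schools.
3. Report eCO sensitivity by smoking frequency, including the most frequent smokers.
4. State that agreement will not be taken on its own as evidence for raising a cut-point.

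The cost is wording and a few extra tables, with no new measurement. The drawback is a smaller reference sample: about 4 × 333 = 1,332 control students per country before selection.
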